### Justification for the proposed dose, route of administration, dosage regimen and treatment period

The starting dose for the oral single ascending dose stage will be 300 mg. This is a routine dose recommended for the treatment of heavy metal poisoning
^
38,
39
^. The maximum dose that will be administered during the oral single ascending dose stage will be 1,500 mg. This dose has been selected based on pre-clinical in-vitro assays that have shown that high concentrations of unithiol are required to inhibit the pro-coagulant effects of snake venom
^
21
^. In this experiment, 150 µM of unithiol was required to prevent consumption coagulopathy. Given that previous in-human pharmacokinetic analysis has identified a C
_max_ of 25 µM following administration of 300 mg oral
^
33
^, it has been estimated that a dose of 1,500 mg would be required to achieve a peak plasma concentration sufficient to inhibit coagulopathy. Published reports of dose levels of unithiol equivalent or higher than 1,500 mg oral suggest that this dose is safe
^
24,
31,
32
^.

The dose that will be given to the first intravenous dosing cohort (CIV1) will be 3 mg/kg. This has been selected as it is at the lower range of the routinely recommended dose for acute heavy metal poisoning (3–5 mg/kg)
^
27,
40
^. Previous pharmacokinetic analyses have shown that 3 mg/kg intravenous achieves an initial plasma concentration of 100 µM
^
27
^. At least one further intravenous dosing cohort will be included. The dose administered will be decided by the DSMB based on emerging data from the first stage of the trial. This dose is expected to be 5 mg/kg, although a dose of up to 10 mg/kg may be selected, depending on emerging safety and pharmacodynamic data.

For the multiple dosing cohorts (CM1 and CM2), the study team will select doses that show the optimum profile for treating snakebite, based on safety, tolerability and any available pharmacokinetic and pharmacodynamic data. If the pharmacodynamic data shows a dose response relationship and is deemed to demonstrate sufficient reliability, the investigators will aim to select CM1 based on a minimum dose associated with adequate

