### Pharmacodynamics

An exploratory outcome is to assess the efficacy of unithiol to inhibit the pathogenic actions of venom,
*ex vivo*. If the pharmacodynamic assay produces results that are deemed reliable, then pharmacodynamic data from the single dosing stage could be used to guide the dosing regimen for the multiple dosing stage. If the pharmacodynamic assay does not produce useful results, then dose and dosing frequency decisions will be made based on safety and preliminary pharmacokinetic data.

*Ex vivo* assays will be developed for the purposes of establishing a dose-response and estimating a pharmacodynamic profile. These assays will rely on spiking subjects’ plasma with venom
*ex vivo* and measuring activity of snake venom metalloproteinases. These assays are being developed for the purposes of this study, and a published validated assay does not exist. It would not be appropriate to assign these assays as primary outcome variables as they are experimental and represent an indirect estimate of efficacy.

These assays will continue to be refined during this study. They primarily represent a tool to compare venom metalloproteinase inhibition between subjects receiving different doses of unithiol, rather than a direct measure of efficacy. Where possible, these assays will be conducted and refined in the laboratory facilities at KEMRI-CGMRC. Split samples will also be shipped to Liverpool School of Tropical Medicine Centre for Snakebite Research & Interventions (LSTM CSRI).

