### Pharmacodynamics

Pharmacodynamic outputs will vary between assay and are exploratory. For the fluorogenic substrate assay the area under the fluorescence-time curve will be compared between dosing groups using ANOVA and an appropriate post-hoc test (e.g., Tukey’s). The time to plateau and time to mid-point of fluorescence (Km) of the fluorescence-time curves will also be compared with this approach. These same measures will be calculated for the plasma clotting assay. Further assays will be developed, and analysis will be planned as appropriate.

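### Time to plateau and time to mid-point can go unreached or level off under strong inhibition, and ANOVA does not suit such values; the label Km is also wrong (minor)

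*Protocol article*

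**What the plan says.** The Pharmacodynamics paragraph of the Statistics section names three measures for the fluorogenic assay. The first is area: "the area under the fluorescence-time curve will be compared between dosing groups using ANOVA and an appropriate post-hoc test (e.g., Tukey’s"). The other two are times: "The time to plateau and time to mid-point of fluorescence (Km) of the fluorescence-time curves will also be compared with this approach". For the second assay it adds: "These same measures will be calculated for the plasma clotting assay". The paragraph opens with a limit on all of this: "Pharmacodynamic outputs will vary between assay and are exploratory".

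The Pharmacodynamics part of the section on assessment of pharmacokinetics and pharmacodynamics gives the purpose: "They primarily represent a tool to compare venom metalloproteinase inhibition between subjects receiving different doses of unithiol, rather than a direct measure of efficacy". It also says of the assays: "These assays will continue to be refined during this study". If the results are deemed reliable, "pharmacodynamic data from the single dosing stage could be used to guide the dosing regimen for the multiple dosing stage". The dose justification ties this to one cohort: "the investigators will aim to select CM1 based on a minimum dose associated with adequate" ex vivo inhibition of the metalloproteinases. CM2, by contrast, is set by safety and tolerability in single dosing.

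The article gives no reading time, no definition of plateau or mid-point, and no rule for a curve that reaches neither.

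**The concern.** Fluorescence levels off when the substrate is used up. An inhibitor slows the rise, so the better the drug works, the later the plateau and mid-point come, and reading stops at some fixed time. Two things can then happen:

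- If the times are defined against the true plateau, strongly inhibited samples have no value. The value is missing because the drug worked.
- If they are defined against the highest value seen during reading, every sample has a value, but strongly inhibited curves are nearly straight lines and their times converge to the same number.

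A plasma sample that does not clot within the reading raises the same problem. ANOVA is not built for censored values or for values piled up at a ceiling. At stake is the ability of these two measures to tell strongly inhibiting dose levels apart.

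Separately, Km is the Michaelis constant, a substrate concentration. It is the wrong name for a time.

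**Working it through.** The protocol gives no figure for this analysis, so there is none to reproduce. The check is a model of the mechanism.

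**Inputs from the protocol.** The three measures and ANOVA (Statistics, Pharmacodynamics); cohorts of 8 (Dose).

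**Assumptions, because the protocol does not give them.** First-order product curve F(t) = Fmax(1 − exp(−kt)), read from 0 to T. Inhibition I multiplies the uninhibited rate k0 by (1 − I). Plateau means 95% of the maximum. The uninhibited curve plateaus at a fraction f of T, so k0·T = ln(20)/f; f is varied from 0.1 to 1.0.

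**1. Times against the true plateau.** Time to plateau is ln(20)/k, which exceeds T when I > 1 − f. Time to mid-point is ln(2)/k, which exceeds T when I > 1 − f·ln(2)/ln(20) = 1 − 0.231f.

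| f | plateau unreached above | mid-point unreached above |
|---|---|---|
| 0.10 | 90% | 97.7% |
| 0.25 | 75% | 94.2% |
| 0.50 | 50% | 88.4% |
| 1.00 | 0% | 76.9% |

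The two measures are not equally exposed: the mid-point survives much further.

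**2. Times against the observed maximum.** With Fobs = 1 − exp(−kT), the mid-point is −ln(1 − 0.5·Fobs)/k and the plateau is −ln(1 − 0.95·Fobs)/k. As k falls the curve becomes linear and these tend to 0.50T and 0.95T. Area as a share of its maximum is 1 − (1 − exp(−kT))/(kT). Early slope is proportional to 1 − I. For f = 0.5:

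| I | mid-point / T | plateau / T | area | early slope (relative) |
|---|---|---|---|---|
| 0% | 0.115 | 0.492 | 0.834 | 1.00 |
| 50% | 0.215 | 0.777 | 0.683 | 0.50 |
| 80% | 0.358 | 0.909 | 0.417 | 0.20 |
| 90% | 0.426 | 0.933 | 0.248 | 0.10 |
| 95% | 0.463 | 0.942 | 0.136 | 0.05 |
| 99% | 0.493 | 0.949 | 0.029 | 0.01 |

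From 0% to 90% the mid-point rises 0.426/0.115 = 3.7-fold, so it is informative there. From 90% to 99% it rises only 0.493/0.426 = 1.16-fold. Over the same step area falls about 8.4-fold (unrounded values) and early slope 10-fold.

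Area has a weak end of its own, at low inhibition with a long reading: at f = 0.1 it moves only from 0.967 to 0.867 between 0% and 75%. That is the reason to pair it with early slope.

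**3. Simulation.** Groups of 8, f = 0.25, log-SD 0.3 on k, 5,000 runs. Share of samples with an unreached time at 50/80/95/98% inhibition:

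- time to plateau: 1%, 77%, 100%, 100%
- time to mid-point: 0%, 0%, 69%, 100%

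Share of runs in which a two-group t-test (8 v 8, p ≤ 0.05) separated 95% from 98% inhibition:

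- area: about 100%
- mid-point capped at T: 11%; plateau capped at T: 0%
- mid-point against observed maximum: 99.6%; plateau against observed maximum: 52%

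Area and the observed-maximum times carried added measurement noise of SD 0.01 (times in units of T); the capped times carried none. The 99.6% shows that compression alone need not lose the difference if the reading is that precise. The severe loss comes from unreached times.

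**4. Does the trial reach strong inhibition?** The dose justification cites 150 µM in vitro for preventing coagulopathy. Linear scaling (an assumption) from 300 to 1,500 mg oral gives 5 × 11.9 = 59.5 µM using the Table 1 peak, or 5 × 25 = 125 µM using the peak in the dose justification. From 100 µM at 3 mg/kg intravenous, 5 to 10 mg/kg gives 167 to 333 µM. These values lie on both sides of 150 µM, and none is a measured inhibition in these assays.

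**The case against.** The strongest reply is that little rests on these two measures. Area is named first and the times are additional. The outputs are declared exploratory and the assays are still being refined. Single-dose escalation does not depend on them. Their use for CM1 is conditional on reliability, with a fallback to safety and preliminary pharmacokinetics. Reading time, the definition of plateau and a rule for unreached curves are details that the separate analysis plan may hold. All of this stands, and it keeps the point minor. It does not correct the label Km. Nor does it make ANOVA, which the article itself names, a suitable test for times that may be censored.

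Three stronger readings are tempting, and the documents support none of them.

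- A reader might infer that the best dose levels will lose data or look alike. That depends on reading time, plateau definition and inhibition achieved, none of which is given. The article also nowhere says that unreached curves will be dropped.
- A reader might infer that both times are poor measures in general. Below the thresholds above they rise steadily with inhibition and are informative, the mid-point over most of the range.
- A reader might infer that the bias falls where the dose is chosen. CM1 is to be the minimum dose with adequate inhibition, so the relevant boundary is between inadequate and adequate. A measure that levels off among strongly inhibiting doses can still mark that boundary. CM2 does not rest on these measures.

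**Conclusion.** The point holds as a minor one. The article commits to ANOVA on two times that, with a finite reading, may be unreached or converge to a constant under strong inhibition. In the model, the inhibition at which this starts runs from 0% to 90% for time to plateau and from 76.9% to 97.7% for time to mid-point, depending on how early in the reading the uninhibited curve plateaus. The thresholds rest on an assumed first-order curve and a 95% plateau rule; the direction of the problem does not depend on the exact values. Area under the curve, already planned, keeps falling through the range where the times fail. The label Km is an error on any assumption. The consequence is confined to secondary measures of an exploratory outcome, whose use for CM1 is conditional.

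**What to change.** In the Pharmacodynamics paragraph of the Statistics section:

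1. Rest the fluorogenic comparison on the planned area, over a stated fixed reading time, plus the early slope. Keep the two times as supportive only.
2. Wherever a time measure is kept, including the clotting assay, define it. Treat a value not reached as right-censored at the end of reading, ranked longest, and compare groups with a rank-based or censored-data test instead of ANOVA.
3. Delete the label Km.

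The same recorded curves are re-read, so no new samples or assays are needed. The cost is slightly more analysis work, and some loss of efficiency of the rank test if every curve does reach its plateau. One limit remains: if two groups are wholly unreached, their times are all tied and no test on times can separate them, which is why area and slope should carry the fluorogenic comparison.

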### Demographics and baseline characteristics

Demographic data will include age, gender, and race. Baseline data will include medical history, drug history, height, weight, full blood count, renal function, liver function and electrocardiogram. These will be presented using tables and descriptive statistics. Continuous variables will be described using means, standard deviations, medians, and interquartile ranges, as appropriate. Categorical data will be presented as counts and percentages. Missing data will be presented.

### Safety analyses

Adverse event frequency, severity grade (mild, moderate, or severe), and relationship to IMP (no relationship, unlikely, possible, probable, and definite) will be described and reported to the DSMB before any dose escalations. These will be presented by organ system involved and clinically appropriate terminology will be used. Changes to alanine aminotransferase (ALT), plasma creatinine, haemoglobin, white cell count and platelet count will be presented to the DSMB at every safety review. Grading of laboratory values will use the Division of AIDS (DAIDS) Table for Grading the Severity of Adult and Paediatric Adverse Events version 2.1 July 2017
^
42
^. These scales are not based on a coastal Kenyan population. We have modified these for several of our SERU approved trials (R21 (SERU 3711), S4V01 (SERU 3796, CHMI-SIKA (SERU 3190)) to ensure grading reflects normative values in our population.

### Amendments to the statistical analysis plan

Minor amendments to the statistical analysis will be made by the investigator/supervisor/statistician. Any changes that significantly affect the protocol or reporting of adverse events will require approval from the sponsor and research ethics committees and regulatory authority.

## Data management

The data management plan has been uploaded to the Harvard Dataverse (
https://doi.org/10.7910/DVN/LJOYSO). The PI will have overall responsibility for managing the data. A designee to the PI will be responsible for receiving, entering, cleaning, querying, analysing, and storing all data from the study. Responsibility for this may be delegated to the study data management team.

### Data capture methods

Data will be entered into the participant’s paper CRF and subsequently transferred to an electronic database for analysis. A clinical quality management plan (CQMP) will be developed prior to the trial commencing. This will outline the processes for evaluating appropriate use of consent forms, CRFs and any study specific procedures (SSPs).

A laboratory analytical plan (LAP) will be developed prior to the study commencing. Lab samples will be tracked, and clinical results will be reported using the electronic system.

### Archiving

The investigator must keep the consent forms and trial master file for at least 10 years after the completion or discontinuation of the trial. The anonymized electronic databases will be maintained beyond this period.

### Missing data

Missing data will be recorded as such using appropriate coding that is compatible with statistical software. Missing data that impacts on the validity of the results will be clearly reported in scientific publications of this work. Records will be kept detailing the reason for any missing data and occurrence of missing data will be kept to a minimum.

### Patient data protection/confidentiality

All study data for analysis will be de-identified. Participants will be identified via their unique study number. Paper records containing study data will be stored in a locked filing cabinet in a lockable study office. Electronic data will be stored on laptops approved by KEMRI-CGMRC IT department and will be password protected with encrypted hard-drives. Data will be backed up on the KEMRI-CGMRC cloud storage system, which is secured with password protection and approved for use for clinical research data. Participant information will only be shared with those directly involved in conducting this trial. The master list of participant identifiable information will not be removed from the KEMRI-CGMRC site where it will be stored in a locked cabinet in a lockable office.

### Archiving and record retention

Hard copies of documents will be kept for a period of 10 years following completion of the trial. Data and clinical samples will be kept for 15 years at KWTRP. Samples sent to the UK will be kept for a maximum of 10 years and then either destroyed or returned to KWTRP.

## Data sharing

•      Data will be shared with LSTM Centre for Snakebite Research & Interventions (CSRI) and the University of Liverpool, and this will be stated on the consent form and patient information leaflet.

•      Liverpool School of Tropical Medicine is the Sponsor

•      Prior to transfer of data, participants’ names and other identifiable information will be removed.

•      Data will only be accessed by individuals with a direct role in conducting this research.

•      Access by others would require appropriate approvals including from SERU.

•      Data published in peer-reviewed journal and presented at scientific meetings will be available open access. Participants will not be identifiable from the data presented.

## Study monitoring

Regular monitoring will be performed according to International Council for Harmonisation (ICH) Good Clinical Practice (GCP) and a Monitoring Plan. Monitors will check whether the clinical trial is conducted, and data are generated, documented, and reported in compliance with the protocol, GCP and the applicable regulatory requirements. The site team led by the PI will be responsible for local submissions to the regulators and all the staff will have good clinical practice training prior to study start. The PI will give direct access to study documents for monitoring and auditing.

## Quality control and quality assurance

The study team at the trial site will conduct regular quality checks to ensure that the trial is being conducted, data is being recorded, analysed, and accurately reported according to the protocol, trial standard operating procedures (SOPs) and the clinical quality management plan, and in compliance with ICH GCP. Audits will be conducted in the laboratories according to an agreed audit schedule.

## Ethics

Approval will be sought from the CGMRC Centre Scientific Committee (CSC, Kilifi KEMRI Scientific & Ethics Review Unit (SERU), LSTM research and ethic committee (REC) and the Pharmacy and Poisons Board. Written informed consent will be obtained from each participant.

### Human Subjects

As this trial will involve human subjects, the following guidelines will be observed:

“First, do no harm.”

The Investigators are aware that this phase I trial exposes risk to healthy participants. Unithiol is a medication which has been used in humans for several decades and has reassuring safety data. Higher doses than have previously been administered will be used. The animal data suggests low toxicity at higher dose levels, as does the limited data from small observational reports in humans. Additional precautions will be undertaken during administration of higher dose levels, including sentinel dosing. Close monitoring will be in place for the 24-hours after dosing, and after this time plasma levels of unithiol are anticipated to be negligible. As data exist describing the adverse event profile of unithiol in humans, participants will be made aware of the solicited adverse events and early presentation to the study will be encouraged and supported if they occur. Trial insurance through the Sponsor will be in place and will cover the costs of treating any adverse events at appropriate government health facilities. As well as the risks that have been described above and in section 4 (safety data), there will be certain inconveniences. Subjects will be expected to reside at the in-patient facility during dosing and will be asked to attend follow-up appointments. Remuneration will be provided in accordance with KEMRI reimbursement guidelines. Volunteers will be made aware, during consenting, of their responsibilities and the inconveniences involved in becoming a study participant.

### Direct benefit to study subjects or the community

There are limited direct benefits to those involved. The screening process may identify health conditions that would otherwise have gone unnoticed (such as high blood pressure or diabetes), and thus allow for earlier treatment. There may be some perceived benefits although this will just be close clinical monitoring during the trial.

There may be benefit to the local community if this compound were found to be effective in treating snakebite, although it should be noted that the research so far has suggested the strongest benefit would be seen for victims of a snake that reside in West Africa. West Africa is home to a type of snake (
*Echis ocellatus* or saw-scaled viper) that causes many bites that result in uncontrolled bleeding. The experiments of unithiol in mice showed that the drug worked best against the venom of this snake. Further experiments of this drug for snakes that exist in Kenya are being undertaken. The target of this drug (SVMPs) is predominant in most viper species, and it is feasible that this drug may have efficacy for species relevant to Kenya, such as the puff adder.

Conducting the trial in Kilifi will provide a platform for further trials of new treatments for snakebite to be tested.

### Community considerations

KEMRI-Wellcome has a dedicated team which coordinates all engagements with the programme. A CAST (Communication Advice for Studies) group will be formed and will develop a community engagement plan. The cast group will be composed of community liaison group (CLG) and study team members.

Kilifi North and South sub-County Hospital Management Teams (SCHMT) and Pwani University will be approached and informed of the study protocol.

Members of the Kilifi County living in Ngerenya, Chasimba and Kilifi township will be approached through community engagement activities. KWTRP personnel will raise awareness of the trial with permission of community leaders. There will be sensitization through the health management teams and village elders. Following this barazas will be held. At community meetings, focused pertinent information will be provided including the purpose, risks, duration, monetary compensation, exclusion criteria and inclusion criteria of the trial. Interested individuals will have ample time to read the PIS prior to consent. Those interested in the trial will be given written patient information in the appropriate language. 

